### Aim of the study

The aim of this pilot study is to inform a definitive randomised controlled superiority trial. The objectives are:To assess recruitment rate, level of study attrition and the robustness of engagement measuresTo provide an effect size predictionTo get a better understanding of the extent to which participants are engaging with the modules and the bulletin board so that threshold levels of adherence can be refinedTo identify the challenges of conducting research and delivering an online intervention in the workplace

## Methods

### Study design

A three-arm randomised controlled trial (RCT) will be conducted to compare engagement and effectiveness of a minimally guided, online, CBT-based stress management intervention (WorkGuru) delivered with and without an online facilitated bulletin board. Both active conditions will be compared with a wait list control group (WLC). All participants will have unrestricted access to Care as Usual (CAU), such as counselling and medication, which will be monitored to control for potential confounding effects. The trial will be conducted and reported in line with Consolidated Standards of Reporting Trials (CONSORT) 2010 guidelines [31]. A completed Standard Protocol Items: Recommendations for Interventional Trials (SPIRIT) 2013 Checklist (Additional file 1) and chart (see Table 1) have been completed and submitted for publication. Online assessments will be conducted before randomisation, at 2 weeks (credibility/expectancy measure only), on completion of treatment (8 weeks) and at 16-week follow-up (see Fig. 1).

**Table 1 Tab1:** Standard Protocol Items: Recommendations for Interventional Trials (SPIRIT) schedule of enrolment, interventions and assessment

	Study period (weeks)								
Time point	3/16	4/16	5/16	6/16	7/16	8/16	9/16	10/16	11/16
Enrolment									
Recruitment	X	X	X	X					
Eligibility screen	X	X	X	X					
Informed consent	X	X	X	X					
Allocation	X	X	X	X					
Interventions:									
Discussion group	X	X	X	X	X	X			
Minimal support group (MSG)	X	X	X	X	X	X			
Wait list control group (access to MSG)					X	X	X	X	X
Assessments									
T1	X	X	X	X					
Credibility/expectancy	X	X	X	X	X				
T2			X	X	X				
T3					X	X	X		
Study completion									X

**Fig. 1 Fig1:**
[figure not shown]
Study flow chart

### Recruitment and randomisation

Six UK-based organisations will be approached to participate in this study. A sample size of 90 study participants will be recruited from the participating organisations. The sample size of 30 participants per arm is based on the optimum number of discussion group participants identified by WorkGuru, and is equal to the medium per arm sample size identified in an audit of sample sizes for pilot and feasibility studies [32]. Participants will be recruited through advertisements distributed via email, the organisations’ intranets and in-house magazines. All marketing information will include an email address inviting people who are interested in participating in the study to access information made available online or by emailing the first named author (SC). An information leaflet and a link to the online screening questionnaire, the short-form version of the Perceived Stress Scale (PSS-10; [33]) will be made available to all people who express an interest in the study. People who meet the inclusion criteria will automatically be sent a link to the online baseline questionnaire. The online questionnaires will be designed and distributed using Qualtrics survey software. Participants who complete the baseline questionnaire will be randomised. The first author will create an allocation schedule using a computer-generated randomisation sequence (random.org). An independent researcher not otherwise involved in the research will allocate each group (A, B or C) as an active condition (with or without a facilitated bulletin board) or as the WLC. Participants will be randomly allocated on a ratio of 1:1:1 to these groups. The study researchers will be blind to the group allocation.

Randomisation is being conducted at an individual level rather than at organisation or team level. This allows us to control for group stressors such as large-scale redundancies and team deadlines. One of the risks of individual-level randomisation is contamination between the groups (i.e. participants in the WLC talking with participants in an active intervention). The extent of contamination between the study groups will be monitored.

Participants using the bulletin board will be required to use a pseudonym to maintain researcher blindness. Individual-level randomisation has been chosen to control for group stressors (i.e. organisational, department or team change).

### Inclusion and exclusion criteria

Inclusion criteria will be: age 18 years or over, employed by participating organisation, willingness to engage with an online CBT-based stress management intervention, access to a computer or tablet, access to the Internet, and a score of ≥20 on the PSS-10. No exclusion criteria have been set.

### Intervention

The online CBT-based stress management intervention WorkGuru is presented on a secure platform that participants log on to using email addresses and a self-generated password. WorkGuru is a modular intervention that is based on the psychological principles of CBT, positive psychology, mindfulness and problem solving. It has been designed to increase self-awareness, improve flexible thinking and teach active coping skills. There are 10 modules that individuals can select to complete (see Table 2 for more information). Seven of those modules comprise the core modules, which all participants will be advised to complete. The modules consist of a combination of educational reading and audio, short animations, and interactive exercises. Participants can complete a questionnaire and receive suggestions for modules that they may find useful, or they can chose the modules themselves. As well as the modules, participants can complete eight self-monitoring standardised questionnaires, for example: the Perceived Stress Scale [33], the Subjective Happiness Scale [34] and the Brief Resilience Scale [35]. Participants have the option to opt in to a weekly email (the Monday Morning Message) that will reinforce messages of positive thinking and healthy working practices. They can also set themselves email reminders to visit the site. To encourage engagement, the coach will contact each participant through the site three times during the course of the 8-week programme (when an account is created, at 2 weeks and at 6 weeks). Participants can chose to share their work with the coach, and to contact the coach at anytime through the site to ask for feedback or additional help or advice. The coach will respond within 24 h. The coach has a postgraduate-level qualification in executive coaching.

**Table 2 Tab2:** WorkGuru modules

	Module title	Module content	Suggested completion time
1.	Learn about me and my values^a^	Two questionnaires designed to help identify and prioritise work and life values. Exercise to prioritise those values	70 min
2.	Identify the things that cause me stress^a^	Psychoeducational information on stress, a Stress Diary and an exercise designed to help individuals analyse their stress diaries looking for patterns to their stress trigger, and the helpful and not so helpful ways they respond to stress	90 min (plus Stress Diary)
3.	Recognise the early warning signs of stress^a^	Psychoeducational information on stress and an exercise to help identify physical, psychological and behavioural symptoms of stress	20 min
4.	Learn about how I think^a^	Brief CBT including cognitive restructuring, automatic thoughts and unhelpful thinking styles	30 min (plus Thought Diary)
5.	Resilience: learning to bounce back^a^	Psychoeducational material on positive psychology and nine ‘happiness’ exercises focussing on increasing positive thinking	40 min (plus exercises to be completed over a number of weeks)
6.	Manage my stress^a^	Identifying and reducing the demands that are being made, and increasing the capacity to cope with those demands.	60 min
7.	Working smarter not harder^a^	Exercise and psychoeducational material on prioritising, focussing energy, learning to let go and time management	90 min (plus an option of a diary)
8.	Think about where I want to be in the future	Exercises to help imagine the best possible self and steps needed to get there	30 min
9.	Mindfulness	An introduction to mindfulness with guided meditations	90 min
10.	Explore creative ways to problem solve	Exercises introducing problem solving techniques	60 min

Note: ^a^Core module

Throughout the content of the WorkGuru website, users are prompted that if they are concerned about their mental health they should speak to their GP, NHS 111 or the Samaritans. Contact details are given.

### Minimal support group (MSG)

The MSG will have full access to the intervention as described above, including direct messaging support from the coach.

### Online discussion group

As well as accessing the online modules, and the direct messaging support from a coach, the online discussion group will also have access to an 8-week online facilitated discussion group delivered via a bulletin board. The discussion group will be facilitated by a coach in groups of 30. The coach will introduce one or more modules each week and encourage discussion about the topic. Participants will be required to select a user name, so that they will be anonymous in the group.

### Wait list control group (WLC)

The WLC will have access to the minimal support intervention (the online modules and direct messaging support from a coach) after 16 weeks.

### Measures

#### Screening measure

A score of ≥20 on the PSS-10 has been identified as inclusion criteria for this study. The cut-off of 20 represents 1 standard deviation (6.35) above the mean (13.02) in a large (*n* = 2387) US general population sample [36]. PSS-10 was chosen because it was felt that stress was something that employees could readily relate to (as opposed to anxiety or depression), and it is a widely used and validated scale that has been designed to measure the extent to which individuals perceive aspects of their life in that last month as being uncontrollable, unpredictable and overloading. In a review of the scale Eun-Hyun [37] reported a Cronbach’s alpha and a test-retest reliability of > .70. The author concluded that the psychometric properties of PSS-10 are superior to those of PSS-14, and recommend that PSS-10 should be used both in practice and research.

#### Primary and secondary outcome measures

The primary outcome measure of the study is engagement (the number of logins to the site); the secondary outcome measures include further engagement measures (the number of pages visited, the number of modules completed, and self-report engagement) and measures of effectiveness (the English language short-form version of the Depression, Anxiety, Stress Scale (DASS-21; [38]) and the wellbeing at work indicator (IWP Multi-affect Indicator; [39])). The DASS-21 has been designed to measure the negative emotional states of depression, anxiety and stress. In a review of the scale Henry and Crawford [40] reported a Cronbach’s alpha of .93. The scale was described as moderately sensitive to change in a clinical sample of depressed subjects [41]. The IWP Multi-affect Indicator is a 16-item measure of subjective wellbeing at work. Alpha coefficients for this scale range from .75 to .90 [42].

#### Other measures

Client Satisfaction Questionnaire [43]. The CSQ is an eight-item questionnaire that has been developed to assess general satisfaction with services. It has a high degree of internal consistency (*α* = 0.93; [43]).

A six-item questionnaire developed to rate the acceptability of cCBT was adapted from Schneider et al. [44]. Participants were asked to rate the following statements on a five-point scale where 5 is ‘strongly agree’:I can use the computer at my own paceUsing a computer is anonymous. I don’t need to tell people about my problemsIt is convenient for me to access help via the Internet and not to have to go to a health centre or clinicI can access help at a time to suit meThe computer will not criticise meAccessing support online is as acceptable as visiting a counsellor or other mental health professional

The credibility/expectancy questionnaire was developed by Devilly and Borkovec [45] to measure treatment expectancy and rationale credibility for the use in clinical outcome studies. An adaptation of the wording was made to replace ‘therapy’ with ‘programme’ and ‘trauma symptoms’ with ‘stress symptoms’. The authors reported high internal consistency (*α* > 0.84) and good test-retest reliability (*α* = 0.82 for expectancy and *α* = 0.75 for credibility).

The Online Support Group Questionnaire [46] was used to assess participants’ experience of the group. The authors report Cronbach alphas of the Support, Relevance and Comfort subscales as *α* = 0.84, *α* = 0.77 and *α* = 0.82, respectively.

The System Usability Scale [47] is a 10-item questionnaire which measures a subjective rating of a product’s usability. The test has demonstrated good reliability (*α* = 0.91; [48]).

The time perception measure [49] is a five-item questionnaire that has a good level of reliability (*α* = 0.89). Participants are asked to indicate on a five-point scale (originally presented by Etkin et al. as a seven-point scale) where 5 is ‘strongly agree’, the extent to which they agree with the following statements:I have a sense that time is expandedI have a sense that time is boundlessI have a sense that time is constrictedI always feel as if I am in a rush/hurryI always feel as if I do not have enough time

The Goal Conflict Index (developed for this research) is a three-item questionnaire that asks participants to indicate on a five-point scale where 5 is ‘strongly agree’ the extent to which they agree with these statements:I often feel torn between my work and my home lifeI often have a number of competing duties that pull on my timeIt is often difficult to prioritise between the different goals in my life

Job autonomy is measured using the nine-item autonomy subscale of the more comprehensive 77-item Work Design Questionnaire [50]. The authors report good internal consistency for the autonomy subscale (*α* > 0.85).

To test whether the programme targets a pressing concern, we have included the question: ‘On a scale of 1–10 how important is it to you to reduce your level of workplace stress?’

As recommended by Rozental et al. [51], we have included a question to identify any possible negative effects of the intervention. Deterioration between pre and post treatment will be reported, and the self-report question: ‘What, if any, positive or negative effects caused by the programme/being in the control group did you experience?’ will be asked. Existing psychological illness will be monitored with the question: ‘Have you received a diagnosis of mental illness from your GP or a health care professional?’ Contamination between the groups will be monitored with the question: ‘During the course of this study to what extent have you discussed the research with colleagues who were allocated a different research group? (For example, if you are in the control group have you spoken with colleagues who are using the online programme?)’.

CAU (including medication for depression or anxiety) will be monitored using the Client Service Receipt Inventory ([52]; adapted for this study). The CSRI was developed to be easily adaptable to the context of the research in which it is being used [53].

Previous experience of stress management training will be monitored with the question: ‘Have you previously received stress management training including training on relaxation techniques and time management?’ To assess levels of sickness absence, participants will be asked if they had taken time off work for a stress-related complaint in the previous 8 weeks at time points 1, 2 and 3.

Demographics will include: age, gender, fluency of written and spoken English, country of birth (UK, non-UK), relationship status, work role, number of working hours (low, middle, high), organisation, education level, income bracket and familiarity with online environment. The full list of measures is depicted in Table 3.

**Table 3 Tab3:** Measures

Measure (number of items)	T1	T2	T3
Primary measure: engagement			
Number of logins to the website		(X)	
Secondary measures: engagement			
Number of modules completed		(X)	
Number of pages visited		(X)	
Self-report engagement		(X)	
Secondary measures: effectiveness			
DASS-21 (21)	X	X	X
IWP Multi-affect Indicator (16)	X	X	X
Other measures			
Number of visits to discussion group		X^a^	
Number of contributions to discussion group		X^a^	
Existing psychological condition	X	X	X
Messages sent to and from coach		(X)	
Demographics	X		
Care as Usual (2)	X	X	X
Time Perception Index (5)	X	X	X
Goal conflicts (3)	X	X	X
Acceptability (6)	X	X	X
Credibility/expectancy (6)		2 weeks	
Level of importance (1)	X		
Negative effects of treatment (1)		X	X
Job autonomy (9)	X		
System Usability Scale (10)		(X)	
Client Satisfaction Questionnaire (8)		(X)	
Online Support Group Questionnaire (9)		X^a^	
Experience of stress management training (1)	X		
Sickness absence for stress-related complaint (1)	X	X	X
Contamination question (1)		X	X

T1 = baseline, T2 = 8 weeks (completion of intervention), T3 = 16 weeks (follow-up)

Groups: X = all three groups, (X) = MSG and discussion group, X^a^ = discussion group only

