## Background

One in six adults in England meet the diagnostic criteria for at least one common mental health disorder (CMHD), but only 24% of them are receiving any form of treatment [1]. Psychological ill health is the leading cause of sickness absence in the UK accounting for 70 million sick days in 2013 and costing the economy £70–£100 billion per year [2]. Reducing the prevalence of CMHDs is a major public health challenge [1]. One approach to addressing this challenge is to utilise the Internet as a means of delivering evidence-based psychological treatments.

In 2013, 73% of adults in Great Britain used the Internet every day, with 43% using it to seek health information [3]. The Internet has become a natural means for delivering health care information [4], treatment, and prevention programmes [5]. In the UK, computerised cognitive behaviour therapy (CBT) (cCBT) is endorsed by the National Institute for Health and Care Excellence [6] for the treatment of persistent subthreshold depressive symptoms or mild to moderate depression. NICE have also identified cCBT as a promising low-intensity intervention for generalised anxiety disorder [7].

A large number of meta-analyses have found evidence for the delivery of online CBT-based programmes delivered in clinical or community settings for individuals with depression and anxiety [8–12], but the evidence for online psychological interventions delivered in workplace settings is less convincing [13–15].

Researchers have argued that adherence (completing the intervention to the extent that the developers intended it to be used; [16]), engagement (the extent, both in terms of time and frequency, that participants visit the website) and attrition (participants in a study who do not fulfill the research protocol; [16]) all pose challenges to the evaluation and delivery of Internet interventions [17–19]. For Internet interventions delivered in real-world settings (as opposed to clinical research settings), these challenges can be even more acute [20, 21] with as few as 1% of registered users completing all sessions of a freely available online CBT programme for people with panic disorder and agoraphobia [22].

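### The single self-report harm item is not like for like between the active and wait-list arms, and LOCF, if applied to deterioration, counts anyone missing week 8 as not worse

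*Protocol article*

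**What the plan says.** The Protocol article, under Other measures, plans two harm measures in one sentence. The first is a change measure: "Deterioration between pre and post treatment will be reported". The second is a self-report question: "What, if any, positive or negative effects caused by the programme/being in the control group did you experience".

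Table 3 lists the question as one item, at T2 (week 8) and T3 (week 16), with a plain X at both. The key reads "Groups: X = all three groups, (X) = MSG and discussion group, X^a^ = discussion group only", so all three arms are asked. DASS-21 and the IWP Multi-affect Indicator carry a plain X at T1, T2 and T3.

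Study design also has an online assessment "at 2 weeks (credibility/expectancy measure only"), so it carries no harm item. Table 3 does not mark which arms receive that form.

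Statistical analyses says missing data will be imputed by LOCF, and by the group mean for engagement measures with no earlier value. It makes no exception for the deterioration report. The Discussion accepts that participants cannot be blinded to the type of intervention.

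**The concern.** The self-report item has two weaknesses as worded and scheduled.

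- **Attribution.** It does not ask whether anything got worse. It asks what the participant thinks their allocation caused, for good or ill, in one open answer. The named cause is the programme for active participants and control status for the others. A person whose stress rises for reasons they see as unrelated reports nothing in either arm, and the two arms apply different filters.
- **Coverage.** A person who returns neither the week-8 nor the week-16 questionnaire contributes nothing. If LOCF is also used for deterioration, that measure does not recover them: it records them as unchanged.

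The wait-list arm was included because this programme's efficacy is not established and a no-treatment comparison was wanted. The self-report item cannot serve that comparison for harm. A pilot meant to inform a definitive trial would carry forward a harm measure with the same limits.

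**Working it through.** **Inputs from the Protocol article.** 30 per arm in three arms, allocated 1:1:1 (Recruitment and randomisation): 3 × 30 = 90, which reproduces the stated total. One harm item at T2 and T3 (Table 3). LOCF for missing data (Statistical analyses).

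**Assumed, because the documents give no figure.** Dropout of 0% to 50%. A harm report rate of 5%. Deterioration of 10% in those who stay, and 10% or 20% in those who leave. Study attrition is itself a pilot objective.

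**Step 1: what each arm is asked.**

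| Arm | Cause the respondent must name |
|---|---|
| Minimal support | the programme |
| Discussion group | the programme |
| Wait list | being a control |

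The first two rows match, so that contrast is like for like. Either of them against the third is not. No arithmetic is needed.

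**Step 2: information left in the self-report item.** With a share d of an arm missing at both T2 and T3, n = 30 × (1 − d) people answer. If none reports harm, the one-sided 95% upper bound is 1 − 0.05^(1/n). The chance of at least one report at a true 5% rate is 1 − 0.95^n.

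| d | n | Upper bound if none reported | Chance of at least one report |
|---|---|---|---|
| 0% | 30 | 9.5% | 78.5% |
| 10% | 27 | 10.5% | 75.0% |
| 20% | 24 | 11.7% | 70.8% |
| 30% | 21 | 13.3% | 65.9% |
| 50% | 15 | 18.1% | 53.7% |

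These bounds describe people like the responders. They say nothing about those who left, unless leaving is unrelated to harm.

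**Step 3: deterioration if LOCF applies.** A missing T2 score takes the T1 score, so change = 0 and the person counts as not deteriorated. Then:

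- true rate = (1 − d) × q_stay + d × q_leave
- LOCF rate = (1 − d) × q_stay
- share missed = 1 − LOCF rate / true rate

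With q_stay = 10%:

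| d | q_leave | True | LOCF | Share missed |
|---|---|---|---|---|
| 10% | 10% | 10% | 9% | 10% |
| 10% | 20% | 11% | 9% | 18% |
| 30% | 10% | 10% | 7% | 30% |
| 30% | 20% | 13% | 7% | 46% |
| 50% | 10% | 10% | 5% | 50% |
| 50% | 20% | 15% | 5% | 67% |

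The LOCF rate is the value that would hold if no leaver deteriorated, so it is the lowest rate compatible with the observed data.

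**Step 4: unequal dropout.** Take a true rate of 10% in two arms, the same in stayers and leavers, with dropout of 40% and 10%. LOCF gives 0.6 × 10% = 6% and 0.9 × 10% = 9%, so the arm that loses more people looks safer. Observed cases give 10% in both. Observed cases are not a full answer: in the row with d = 30% and q_leave = 20% they give 10% against a true 13%. The number missing therefore has to be shown beside them.

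**The case against.** The strongest reply is that the open item does not stand alone. Deterioration is planned in the same sentence, needs no attribution, and can rest on scales taken in all three arms at all three time points. The item's stated purpose is to identify possible negative effects of the intervention, and asking about cause is a reasonable way to do that. No between-arm test of harm is planned, harm is not among the pilot objectives, and the article promises caution in interpretation. All of this stands. It limits the weight of the point but does not remove the mismatch in wording or the LOCF problem.

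A reader might go further in three ways that the documents do not support.

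- **That the arms cannot be compared on harm at all.** The two active arms answer the same wording, and their contrast isolates the discussion group, the main research variable. Deterioration can be compared across all three arms.
- **That harm in every early leaver is missed.** Table 3 sets no login condition on the item. Someone who stops using the site is still asked at weeks 8 and 16, and someone who misses week 8 can answer at week 16. Only people lost to both give no report. The Background's remark that "these challenges can be even more acute" covers adherence, engagement and attrition together and gives no questionnaire return rate.
- **That harms reported to the coach or on the board will go unrecorded, so a coach log must be added.** An article may leave such procedures to the full protocol. Board users also post under pseudonyms to protect researcher blinding, which complicates a log.

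The scale and threshold for deterioration, and any recall window on the actual form, may likewise be in the full documents. Their absence here is not counted against the plan.

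**Conclusion.** The point holds in a limited form. From the text alone, the self-report item is not comparable between active and wait-list arms, and it gives no information on people who return neither later questionnaire. Deterioration partly fills the gap.

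Whether it does so for people missing at week 8 depends on a condition the article leaves open, namely whether LOCF governs that report. If it does, the share of deteriorations missed equals the dropout rate when leavers and stayers deteriorate equally (10% to 50% over the assumed range). It is larger when leavers fare worse: 18% to 67% if they deteriorate at twice the rate. With no dropout the LOCF problem disappears. All these rates are assumptions, and the direction of any between-arm distortion depends on which arm loses more people.

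This does not touch the primary outcome, number of logins. It is a cheap improvement to harm ascertainment.

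**What to change.** 1. At T2 and T3, in all three arms, first ask one identical neutral item with a stated window, for example: *Since your last questionnaire, have you had any unwanted effect, or has anything got worse? Yes/no; please describe.* Keep the attribution question as the second item.
2. Add the neutral item to the 2-week form wherever that form is sent. If not all arms receive it, report the 2-week answers separately, because the extra reporting occasion would otherwise make the arms unequal again.
3. Report deterioration on observed cases by arm, with the number missing in each arm, beside any LOCF figure.

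The cost is one short item on existing online forms, so slightly longer questionnaires, and one extra line per arm in the deterioration table. No new visit or system is needed.
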